**Fig. 2 Fig2:**
[figure not shown]
CONSORT 2010 Flow Diagram (Anticipated Numbers)

To estimate effect sizes, we compared effect sizes of CET and SST/HOPES from our own data and the SST literature using randomized controlled designs in schizophrenia, bearing in mind the diversity of design and treatment length issues (see Table 1). Given that CET is a composite intervention that includes both cognition, social cognition and social skills interventions, the effect sizes are not surprisingly higher (from .7 after 1 year to > 1.0 after 2 years); SST effect sizes are mostly under .4 in meta-analyses of SST of lengths from 3 weeks to 2 years (and in the HOPES trial did not consistently lessen for one or even 2 years after active treatment). Based on the available studies outlined in the table, we estimated effect sizes of 0.34 (for ICC due to clustering at site level = .01) and 0.37 (for ICC = .02), which justifies our proposed full sample size. With 4 assessments for the full and 5 assessments for three-fourths of the sample, our durability assessment is only somewhat less powerful, with medium effect sizes (from 0.41 to 0.49).

*Accounting for clustering and correlated data.* There are multiple forms of clustering due to participants being nested in sites and repeated observations being nested in participants. Therapeutic groups within a site can also be considered as another level of clustering, but because there are no more than 3 therapeutic groups at any site and they are expected to be led by the same clinicians at the site, we expect little between-therapeutic group heterogeneity within sites and so this level of clustering is unlikely to affect estimates. Nonetheless, we conducted two sets of power analyses, with and without considering therapeutic groups as another level of clustering.

We first only consider clustering effects due to sites and repeated measurement and handle clustering effects as follows: for the correlated nature of data due to repeated measurement, we assumed within-person cross-time correlation to be 0.50 and incorporated this correlation into both analytic modeling procedures (mixed-effects model with random effects) and power calculations. To account for site level clustering effects, we adjusted for sample sizes of 378 individuals by assuming a range of ICC values: 0.01, 0.02 and 0.05. We note the literature reports that in public health and medicine, ICCs in group- or cluster-randomized trials are often small, usually ranging from 0.01 - 0.05 (https://researchmethodsresources.nih.gov/FAQs.aspx). Some statisticians have stated that values of ICCs are usually between 0.01 and 0.02 in cluster randomized clinical studies [78, 79]. Given the multi-determined nature of our health-related outcomes, we believe that the effects due to clustering by site in our study will be small, and thus we adjusted our sample size and power calculations based on two scenarios: assuming an ICC of 0.01 and an ICC of 0.02. After adjustment, our original sample size of 378 reduced to an effective sample size (ESS) of 318 (for an ICC of 0.01) and 274 (for an ICC of 0.02), respectively. Second, for the 3-level clustering effects adjustment, we took account of the 51 therapeutic groups (approximating) as another level of clustering and assumed an ICC due to therapeutic group of 0.01, and adjusted sample sizes by both site and therapeutic group down to 302 and 252, respectively.

#### Power for aim 1

Power analyses for Aim 1 were conducted using Diggle et al. [80] and Lu et al.’s [81] approaches implemented in the LongPower package [82] in R statistical software (version 3.52). Power calculations were conducted to determine minimum detectable differences between arms (CET vs. SST) in changes over time on the primary outcomes. The outcomes for primary hypotheses in Aim 1 are continuous. To detect significantly more improvement for participants in CET than SST with 80% power in the 2-level analysis, the adjusted sample size of N of 318 (with 20% attrition by 12 months) will detect a minimum effect size of 0.34, and the adjusted N of 274 will detect a minimum effect size of 0.37, respectively. Both detectable effect sizes are between small and medium according to Cohen’s d metric for effect size (0.2 = small, 0.5 = medium and 0.8 = large). For the 3-level analysis that includes adjustment for clustering at the therapeutic group level and the adjusted sample sizes of 302 and 252 (everything else is the same), the minimum effect sizes that can be detected are 0.35 and 0.38, respectively.

The full sample of 378 at baseline (thus ICC adjusted sample sizes of 318 and 274) will have 4 assessments (baseline, 6-, 12 and 18 months), but we will also collect data for 284 participants (75% of the original sample of 378) for one extra time point (baseline, 6-, 12-, 18 and 24 months) (thus an ICC adjusted effective sample size for *N* = 284 participants becomes 250—for an ICC of 0.01—and 222—for an ICC of 0.02—respectively, and so the detectable effect sizes with *N* = 250 and 222 with 20% attrition are 0.38 and 0.40, respectively. For the analysis with 3-level clustering (both site and therapeutic group, as well as participants over time), the adjusted sample sizes become *N* = 240 and 208 and the detectable effect sizes with 20% attrition are 0.39 and 0.42, respectively.

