### Study setting and sample

Treatment sites are approximately 24 community mental health centers and hospital outpatient clinics in Massachusetts and eight other states that offer programs for individuals with schizophrenia-spectrum disorders (final list on project website, project-success.net). These sites have been paired by geographic proximity, organizational type, and by race and ethnic proportions in the local community and then randomly assigned to the two study arms, so that the number of participants per arm is approximately equal and the distribution of sites is comparable geographically and unbiased with respect to participant and site characteristics.

Cluster randomization was used to reduce challenges created by the group-based nature of both treatments. We also had several other reasons to reject person-level randomization: increased resources required by participating sites to train two sets of clinicians to implement CET and SST, potential cross-contamination of the two interventions offered within the same setting, and slower accrual of groups in each treatment due to randomization to two different programs.

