### Sample size and power

We expect that each treatment site will enroll on average about 16 participants, yielding a total of 378 participants (see Fig. 2). For all power analyses conducted, based on previous experience, we assumed 20% attrition by 12 months. We further assumed four assessment points (baseline, 6-, 12-, 18- and, for 75% of the sample, 24-month), an alpha level of 0.05, a two-tailed test, with a cross-time correlation of 0.5. We will minimize treatment dropout by reaching out to participants whenever they miss treatment sessions (through the site RA) and by providing makeup sessions (through the site clinicians) that allow those who have missed up to eight sessions to reengage in the treatment without missing content. We will minimize attrition from the research procedures by identifying multiple contact persons when enrolling each participant and by using multiple forms of outreach when a participant is not available for scheduling an assessment or misses a scheduled assessment. Based on our prior experience conducting clinical trials evaluating CET and HOPES (reviewed above), combined with our methods for minimizing attrition, we also believe it is realistic to estimate that the attrition rate for the 1-year durability follow-up will not exceed 20%. However, to be conservative we have estimated our power to detect significant differences between the groups based on a 25% attrition rate.

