### Planned analyses

#### Analysis for aim 1

All analyses will be conducted on the full sample regardless of exposure to treatment (intent-to-treat). Our primary hypothesis in Aim 1 is that CET will be associated with greater improvements than SST in both the *primary outcome*: community functioning (SAS, QLS), and the *secondary outcomes* of neuro- and social cognition (BACS and MSCEIT) and social skills (SSPA). To test this hypothesis, we will fit generalized linear mixed-effects models (GLMM) with identity link functions and a normal distribution specification for both the primary outcome and the secondary outcomes (because both outcomes are measured with interval-level scales). Because patients are nested within site, and repeated observations are nested within participants, we will fit a 3-level mixed-effects model: treatment arm (CET vs SST), time (baseline, 6-, 12- and 18-month) and arm-by-time interactions will be specified as fixed effects. The primary hypothesis of interest will be examined by testing the significance of the difference from zero in the rate of improvement over 18 months (arm-by-time interaction effect). To consider possible variance inflation due to clustering at the site and patient level, site will be treated as a random effect, and the intercept and slope for time at patient level will be specified as random effects. Randomization of sites to implement the CET or SST intervention will be stratified by geographic proximity, such that pairs of sites closest to each other will be randomized to different treatment conditions, and by organizational type and demographic characteristics of the surrounding area. This stratification plan will minimize the impact of any potentially confounding effects on the findings related to the bases of stratification. Because use of stratification may induce correlation between treatment arms, as a recommended cautionary measure, we will adjust for this stratification by including it as a random effect [92].

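### The detectable effects of 0.34 and 0.37 use large-sample critical values although only about 24 paired sites are randomised; on site-level degrees of freedom, power is modestly below the stated 80%

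*Protocol article*

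**What the plan says.** The unit of randomisation is the site. Under Study setting and sample: "Treatment sites are approximately 24 community mental health centers and hospital outpatient clinics". The sites were matched in pairs on geography, organisation type and local demographics, and then randomised. The analysis for aim 1 keeps this structure: "we will adjust for this stratification by including it as a random effect".

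Sample size and power assumes "an alpha level of 0.05, a two-tailed test, with a cross-time correlation of 0.5", and "we assumed 20% attrition by 12 months". Site clustering enters only through an effective sample size, "assuming an ICC of 0.01 and an ICC of 0.02": "our original sample size of 378 reduced to an effective sample size (ESS) of 318 (for an ICC of 0.01) and 274". Power for aim 1 puts these numbers into the LongPower routines and concludes, "with 80% power in the 2-level analysis", that 318 participants "will detect a minimum effect size of 0.34, and the adjusted N of 274 will detect a minimum effect size of 0.37, respectively".

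The same approach gives 0.35 and 0.38 when therapeutic group is added as a level. For the subset followed to 24 months it gives 0.38 and 0.40, or 0.39 and 0.42 with therapeutic group. The section mentions no site-level degrees of freedom, t quantile or correction for a small number of clusters.

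**The concern.** A design effect and a degrees-of-freedom correction do different jobs. The design effect inflates the variance of the arm contrast for within-site correlation. The degrees of freedom reflect how well that variance can be estimated when arm differs only between sites. With 24 sites the usual design-based value is 24 − 2 = 22. With 12 pairs kept in the analysis it is 12 − 1 = 11. The two-sided 5% critical values are then 2.07 and 2.20 instead of 1.96. An effective sample size can therefore be right while the detectable effect derived from it is too small.

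The article uses 0.34 and 0.37 to justify the full sample size, and its Discussion describes the comparison as well powered. The figures should describe the design that was randomised.

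**Working it through.** **Inputs from the article.** Two-sided alpha 0.05; power 80%; cross-time correlation 0.5; 20% attrition by 12 months; N = 378; about 16 per site; about 24 sites in pairs; site ICC 0.01 and 0.02; effective N 318 and 274.

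**Assumptions.** Retention of 1, 0.9, 0.8 and 0.8 at the four visits, compound symmetry, equal arms. Degrees of freedom of 22 and 11 are the design-based values; the article states none.

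**1. Reproduce the stated figures.** Detectable effect = (1.960 + 0.842) × √(4v/N), where v is the variance of the estimated 18-month change. Under these assumptions v = 1.176.
- N = 318: 2.802 × √(4.704/318) = 0.341 (stated 0.34)
- N = 274: 2.802 × √(4.704/274) = 0.367 (stated 0.37)
- N = 302 and 252, with therapeutic group: 0.350 and 0.383 (stated 0.35 and 0.38)

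Normal quantiles recover the article's figures, so the stated 80% behaves as if 318 or 274 people had been individually randomised.

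**2. Same standard error, site-level degrees of freedom.** The noncentrality at the stated effects is 2.802. From a noncentral t distribution:

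| df | Power | Multiplier for 80% | From 0.34 | From 0.37 |
|---|---|---|---|---|
| 22 | 76% | 1.046 | 0.356 | 0.387 |
| 11 | 72% | 1.099 | 0.374 | 0.407 |

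If the other stated effective sample sizes are also accepted, and all sites contribute, the same multipliers apply:
- 0.35 becomes 0.366 or 0.385
- 0.38 becomes 0.398 or 0.418 (it appears for both therapeutic group and 24 months)
- 0.39 becomes 0.408 or 0.429
- 0.40 becomes 0.419 or 0.440
- 0.42 becomes 0.439 or 0.461

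**3. Check the effective N against 24 sites.** Effective N = 378/[1 + (m − 1) × ICC].
- Solving for m: 378/318 = 1.189 gives m = 19.9, and 378/274 = 1.380 gives m = 20.0. That is about 19 sites.
- With 24 equal sites, m = 378/24 = 15.75. Effective N = 378/1.1475 = 329 and 378/1.295 = 292.

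Step 2 therefore joins degrees of freedom from 24 sites to effective sample sizes that imply about 19.

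**4. Consistent 24-site inputs.** Noncentrality = 2.802 × √(329.4/318) = 2.851 and 2.802 × √(291.9/274) = 2.892.

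| df | Power at 0.34, ICC 0.01 | Power at 0.37, ICC 0.02 | 80% detectable effects |
|---|---|---|---|
| 22 | 77.8% | 78.9% | 0.350, 0.375 |
| 11 | 73.8% | 74.9% | 0.367, 0.394 |

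For example, 0.34 × √(318/329.4) × 1.046 = 0.350.

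**5. Credit for matching.** The 11-df rows assume that pairing removes no between-site variance. If it removed half, the 24-site design effect becomes (1 − ICC) + 15.75 × ICC × 0.5, which is 1.069 or 1.138. Power on 11 degrees of freedom is then 76.7% at ICC 0.01 and 80.2% at ICC 0.02.

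**The case against.** **The tested term is arm-by-time.** The planned model names a site random effect and patient-level intercepts and slopes, but no site-level or pair-level time effect. Site and pair intercepts cancel from within-person change, so Kenward-Roger or Satterthwaite degrees of freedom from that model would be on the patient scale. This stands against the remedy: a reader might infer that naming such a method is enough to give 22 or 11 degrees of freedom, and it is not. It does not rescue the power figures. The article's own calculation deflates this same contrast for site ICC, and so accepts that site variation enters it.

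**The size is easily overstated.** A reader might infer from step 2 that power is simply 76% or 72%, and that every detectable effect is 5 to 10% too small. The documents do not support that as a general statement. With 24 equal sites and 22 degrees of freedom, the increases are 2.8% (0.350 against 0.34) and 1.4% (0.375 against 0.37).

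**Pairing is charged its full cost.** Eleven degrees of freedom is the value with pairs as blocks. A pair random effect estimated near zero need not cost that much, and a positive one brings a gain in precision. Step 5 shows that the gain could remove the shortfall at ICC 0.02. The article quantifies no such gain.

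**The choice of method belongs in the analysis plan.** The article's sums do follow from its method, and the choice of degrees-of-freedom method can be left to a document not shown here. The detectable effects, however, are stated here as results, so correcting them is in scope.

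**Conclusion.** The point holds, at modest size. The detectable effects in Power for aim 1 adjust the variance for site ICC but use large-sample critical values for a comparison randomised over about 24 paired sites. On site-level degrees of freedom, and with no credit for matching, power at 0.34 and 0.37 lies between about 72% and 79%. That is 1 to 8 points below 80%; the exact value depends on the site count, the ICC and whether pairs are kept.

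This rests on design-based degrees of freedom for 24 sites or 12 pairs, equal site sizes, and the article's own ICCs. If the site count were really about 19, as the effective sample sizes imply, power would be about 75% unpaired (17 df) and 69 to 70% paired (8 to 8.5 df). If matching is effective, the loss shrinks and can vanish at ICC 0.02.

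A reader might also infer that the trial is seriously underpowered or must enrol more participants. The figures do not show that. The restated effects for 318 and 274, about 0.35 to 0.41, still lie between small and medium on the scale the article uses.

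**What to change.** 1. Restate the detectable effects in Power for aim 1, or the power at 0.34 and 0.37, with t quantiles on site-level degrees of freedom: 22, and 11 if pairs are kept. Include the therapeutic-group and 24-month figures. Any precision credited to matching should be stated as an assumption.
2. Reconcile the site count with the effective sample sizes. Values of 318 and 274 imply about 20 participants per site, whereas the article states about 16 per site at about 24 sites.
3. So that the analysis matches the restated figures, add a site-by-time random effect (and pair-by-time, if pairs are kept) to the arm-by-time model. Test the interaction with a small-sample method such as Kenward-Roger or Satterthwaite. Without the site-level time effect, the method alone will not give site-level degrees of freedom.

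The cost is slightly less favourable stated figures and a few sentences on the model. No additional participants or data are needed.

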### Measures

All interview ratings and cognitive testing will be conducted by trained raters and administered over the web by a project research assistant at the project’s central site, with an on-site RA managing arrangements so that the interviewer is blind to treatment assignment. Participants will be assessed at Baseline, 6 months into the program, 12 months (at completion of the program), 18 months (6 months after program completion), as well as 24 months (12 months after program completion for at least 75% of participants—those whose groups have completed in sufficient time). All data are recorded at the time of assessment in BIDMC’s secure and HIPAA-compliant REDCap system and are subsequently checked for completeness by the project research coordinator.

The outcomes we have chosen include the primary and secondary outcomes identified in prior research on CET and SST/HOPES and represented in our hypothesized causal model (see Table 2). The measures are easy to administer at the community level, endorsed by the stakeholders, relatively brief (total < 2 hours for the overall assessment), and include engaging qualitative questioning as well as fixed choice questions. Since all assessment procedures were adapted for videoconferencing due to the pandemic, several measures from the Penn CNB that can be administered remotely replace corresponding measures in the NIH Toolbox that have not been adapted for remote delivery.

**Table 2 Tab2:** Outcome Measures and Causal Role

Category	Role
**Outcome Measures**	
*PANSS-6*	Negative symptoms
Neurocognition: NIH Toolbox and Penn CNB	Neurocognition
Social cognition: MSCEIT: Managing Emotions	Social cognition
Social Skills Performance Assessment (SSPA)	Social functioning
Community functioning (SAS-II)	Community functioning
Heinrichs Quality of Life Scale	Quality of Life
**Baseline-only measures**	
Diagnosis: MINI	Eligibility
Estimated IQ (from NIH Toolbox)	Moderation

#### Primary outcome measures

*Community functioning* is measured with the Social Adjustment Scale (SAS-II), which has previously been validated as an interview-based measure (utilizing self-reports) of social and community functioning [83]. The SAS-II quantifies adjustment in different roles (e.g., work, school), social and leisure activities, intimate relationships, and overall adjustment. *Quality of life* is assessed with the Quality of Life Scale [84]. This 21-question interview-based, interviewer-rated measure assesses social functioning, role functioning, and motivation, as indicated by items such as sense of purpose, curiosity, and inner drive [85]. To measure symptom severity, we will use a short, validated version of the Positive and Negative Syndrome Scale (PANSS-6, 6 items) [86, 87].

#### Secondary outcome measures

*Neurocognition*. We use a combination of measures from the NIH Toolbox and the Penn CNB that can be administered remotely and that match the 7 cognitive domains in the MATRICS Consensus Cognitive Battery. From the NIH Toolbox: Auditory Verbal Learning Test (verbal memory and learning), List Sorting Working Memory (working memory), Picture Sequence Memory (visual episodic memory and learning), Picture Vocabulary (language), and Oral Reading Recognition (language). From the Penn CNB: Continuous Performance Test (attention/vigilance), Mouse Practice Task (speed of processing), Digit Symbol (speed of processing), Conditional Exclusion Test (executive functioning/reasoning and problem solving). *Social cognition*. We use the Managing Emotions subtest of the Meyer-Salovey-Caruso Emotional Intelligence Test (MSCEIT) which is sensitive to treatment-related change in social cognition [88] and social functioning in SZ [56]. Social skills will be assessed using the Social Skills Performance Assessment (SSPA), a role play test that is audio-recorded and then rated for different dimensions of social skills [89].

#### Process evaluation

We will conduct a process evaluation using mixed methods to assess both intervention delivery and participant experience in each intervention (see Table 3). Treatment delivery will be monitored with three types of data. (1) *Treatment fidelity*: Group sessions are recorded at each site throughout the study and recordings are uploaded to a REDCap database. The recordings are monitored by supervising clinicians (study Co-Investigators) and used for feedback and training; at least six sessions are reviewed during the first 3 months and at least four sessions are reviewed thereafter through the remainder of the twelve-month treatment period. Supervising clinicians will rate at least ten sessions per year for fidelity with respect to each CET and HOPES group, using standard fidelity scales for both treatments that have been adapted to a common 4-point metric [40–42, 45]. (2) *Treatment engagement*: Treating clinicians and site RAs at each site create careful records of all individual and group sessions delivered, patient attendance, and session highlights. These records also include homework completion (CET, HOPES) community trips (HOPES), and makeup sessions (CET, HOPES). The clinicians and site RAs record this information and the site RA enters it in a REDCap database. (3) *Treatment experience*: The supervising clinicians of CET and SST summarize their impression of treatment delivery at each site at 6 and 12 months in qualitative comments; these summaries are captured in a REDCap database.

**Table 3 Tab3:** Selected Process Measures

Process measures	Data collected by
Treatment satisfaction questionnaire (self-rating) [90]	Patient self-rating
Treatment fidelity (checklist)	Supervising clinician
Treatment adherence (provider-based)	Site RA^a^
Simplified Service utilization rating form (SURF) [91]	Research assistant

^a^Site RAs will be trained to collect these data

Participant experience is monitored with both quantitative and qualitative data. (4) *Participant satisfaction*: Participants are sent invitations to complete the Client Satisfaction Questionnaire (CSQ-8), a brief eight item self-report survey, via their mobile device, tablet, or computer once per month, during each month that they are enrolled in treatment [90]. (5) *Participant assessment*: Two randomly selected participants are selected during month-2 of treatment delivery at each site for a qualitative interview using an open-ended interview designed to elicit information about the treatment experience. This process is repeated using a similar open-ended interview schedule for two randomly selected participants in the 11th month of their treatment. (6) *Service utilization*: Participants continue to participate in regular services throughout the intervention, excepting other SST-based or CR-based therapies. A modified version of the Service Use and Resource Form (SURF) pertaining to services received in the past month is completed by participants at baseline and follow-up assessments [91]. (Treatment interruptions due to hospitalization or other events are recorded as part of the treatment engagement record).

We will monitor treatment delivery throughout the project and the project leadership will contact site PIs or other stakeholders as necessary to understand the bases for any indications of problems with treatment quality or quantity. Supplementary training will be provided to clinicians at sites as needed to ensure treatment fidelity and the project leadership group-- including engagement coordinators and staff—will review a summary report based on process measures each quarter to ensure identification of processes in need of improvement. If necessary, we will refine our recruitment and retention strategies based on our quarterly review of patient engagement.

